### Secondary Objectives

- To compare the PFS of patients in the treatment of D2 gastrectomy plus liver radiofrequency plus postoperative chemotherapy to those treated with chemotherapy alone

- To explore a comparison of the total incidence of complications of D2 gastrectomy plus liver radiofrequency plus postoperative chemotherapy to those of chemotherapy alone

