### Randomization Procedure

Eligible participants will be randomly designated to either the test group or the control group in a 1:1 distribution ratio. First, all enrolled patients were tested the molecular profile of the tumors, such as HER2, PDL1, MSI and MMR expression. And after the patient underwent molecular profile testing, patients with HER2-positive advanced gastric cancer were excluded since trastuzumab in combination with chemotherapy has become the standard treatment for these patients. For the rest of the other patients, follow up treatment protocols could be adjusted according to the patients’ molecular profile, such as immunotherapeutic antibody PD-1 or PD-L1, and so on. Accordingly, in the statistical analysis of data, different patients also need to conduct subgroup hierarchical analysis according to the molecular detection results of tumors to reduce data error. Biostatisticians not involved in this study will use SAS software 9.2 (SAS Institute, Cary, NC, USA) to generate random sequences. A research assistant not participating in the recruitment process will seal the random list in sequentially numbered nontransparent envelopes stored in a cabinet that is double-locked. The research assistant will store the randomly assigned envelopes separately. Data collection and data analysis will be blinded, except that the intervention is not blinded to participants and clinicians (16).

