Adverse events are adverse medical events that occur after surgical and medical treatment in patients in clinical trials. Adverse events, whether treatment-related or not, will be considered from the date participants sign informed consent until 5 years after the end of treatment in this study. The nature and severity of adverse events will be assessed in accordance with “expert consensus on diagnostic criteria for postoperative complications of gastrointestinal cancer in China”. The investigator will determine if the adverse event is clinically significant, and if so, it will be identified as an adverse event. The investigators will assess possible relationships among the adverse events, the investigational drugs and the surgery to assess adverse events and their causal relationship to treatment. Adverse reactions include those results recorded as positive, correlated, and possibly correlated. The investigators will keep a full record of serious adverse events from the start of the surgery to the end of the study. All serious adverse events will be reported regardless of whether they are related to the use of drugs or surgery in the study. It is the responsibility of the investigators to notify independent ethics committees or governmental regulatory authorities related to adverse events.

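### Investigators who know the arm decide, with no stated criterion, which events become adverse events, and all are graded on a postoperative standard, so the non-serious event record can differ by arm for reasons other than treatment

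*Protocol article*

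**What the plan says.** All references are to the protocol article.

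- **Scope of adverse events (Study Endpoints).** "Adverse events, whether treatment-related or not, will be considered from the date participants sign informed consent until 5 years after the end of treatment".
- **The gate (same paragraph).** "The investigator will determine if the adverse event is clinically significant, and if so, it will be identified as an adverse event". No grade, threshold or other criterion follows.
- **Grading (same paragraph).** The nature and severity of adverse events are judged by an expert consensus on "diagnostic criteria for postoperative complications of gastrointestinal cancer in China". This is applied to adverse events generally, not only to those after surgery.
- **Attribution (same paragraph).** "The investigators will assess possible relationships among the adverse events, the investigational drugs and the surgery".
- **Serious events (same paragraph).** "All serious adverse events will be reported regardless of whether they are related to the use of drugs or surgery in the study". The full record of serious events is described as running from surgery to the end of the study.
- **Blinding (Randomization Procedure).** "Data collection and data analysis will be blinded, except that the intervention is not blinded to participants and clinicians".
- **Secondary endpoint (Secondary Objectives; Study Endpoints).** One objective is "To explore a comparison of the total incidence of complications" between the arms. The total combines postoperative and chemotherapy complications. Postoperative complications have a 30-day window, Clavien-Dindo severity and several individually defined events. Chemotherapy complications are described only as side effects, with ototoxicity and nephrotoxicity as examples.

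**The concern.** An adverse event record should capture what happened to the patient and leave importance, severity and cause to be coded afterwards. Here the judgement of importance comes first and decides whether the event exists in the record at all. It has no criterion, and the person making it knows whether the patient had a gastrectomy and ablation or chemotherapy alone. A minor complaint might be treated as expected after major surgery in one arm and as a drug effect in the other, or the reverse. The direction cannot be predicted.

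The grading standard adds a second asymmetry. Both arms receive S-1 plus cisplatin, but the only standard named for adverse events was written for postoperative complications. Control patients have no operation, so their toxicity has no suitable scale in this paragraph.

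At stake are the between-arm record of non-serious events and possibly the chemotherapy part of the total complication rate. An event that was never recorded cannot be recovered at analysis. The primary endpoint, overall survival, is not affected.

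**Working it through.** **1. Does the person applying the gate know the arm?** The blinding sentence calls data collection blinded but excepts clinicians. The investigators who apply the gate must also relate events to drug or surgery, which cannot be done without knowing the treatment. The Clinical Data section has medical staff collect the data, including surgery details. So the judgement is unblinded.

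**2. Which events are exposed?** Serious events are to be reported whatever their cause, so the gate bears mainly on non-serious events. One gap remains: the full serious-event record starts at surgery, which leaves its start undefined for controls.

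**3. Does the gate reach the secondary endpoint?** The two components differ.
- Postoperative complications have their own time window, severity system and several event definitions, with no clinical-significance condition. A link to the gate is weak.
- Chemotherapy complications have no grade, threshold or window. They are the only component a control patient can contribute. No other stated rule decides which of them count, so a link is plausible, but the text does not state one.

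**4. The plan's nearest figure.** The plan gives no filtering rate. Its sample size of 178 is built on adverse event rates of 60% and 81.8%, a margin of 5% and 80% power. It reproduces with one-sided alpha 0.05, pooled variance under the null and unpooled under the alternative:

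n = [1.645·√(2·0.709·0.291) + 0.842·√(0.6·0.4 + 0.818·0.182)]² / (0.218 − 0.05)² ≈ (1.057 + 0.525)² / 0.0282, which rounds up to 89 per arm, 178 in total.

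This shows only that adverse event incidence is the quantity on which the trial was sized.

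**5. Illustration (assumed filtering).** Inputs:
- 100 patients per arm (abstract).
- Equal true rates p in both arms. The values tried are 5/7 = 71.4% and 9/11 = 81.8%, from the counts in the sample size section, and the 60% stated there.
- A share f of patients with an event lost from one arm's count only. This f is assumed. It is a share of patients, because incidence counts patients with at least one event. A loss of 10% of events equals a loss of 10% of patients only if each patient has a single event.

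With a = p, b = p(1 − f), m = (a + b)/2, se0 = √(2m(1 − m)/100) and se1 = √((a(1 − a) + b(1 − b))/100), the chance of a two-sided 5% result is Φ((a − b − 1.96·se0)/se1) + Φ((−(a − b) − 1.96·se0)/se1).

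For p = 71.4% and f = 10%: a − b = 0.0714, se0 = 0.0660, se1 = 0.0659, giving Φ(−0.88) + Φ(−3.05) ≈ 0.190.

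| f | p = 60% | p = 71.4% | p = 81.8% |
|---|---|---|---|
| 0% | 5.0% | 5.0% | 5.0% |
| 5% | 7.1% | 8.5% | 11.1% |
| 10% | 13.7% | 19.0% | 28.4% |
| 15% | 24.8% | 35.9% | 52.5% |
| 20% | 39.8% | 56.0% | 75.1% |

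In the other direction, a true difference of 81.8% against 71.4% would disappear if the higher arm lost 1 − (5/7)/(9/11) = 12.7% of its patients with an event.

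**The case against.** Several points on the other side stand.

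- **The endpoint.** A reader might infer that the gate biases the whole total complication rate. The documents do not support that. Nothing says the endpoint is counted from the gated record, and postoperative complications are defined separately without the gate.
- **Contradiction.** A reader might also see a contradiction with the statement that events count whether related to treatment or not. There is none: that statement concerns cause and the gate concerns importance, so both can hold.
- **Serious events.** They are to be reported regardless of cause, so it would be too strong to say that dangerous events will be lost. The start of their full record at surgery is a flaw for controls, but a narrower one.
- **Ascertainment.** The Clinical Data and Follow-up sections schedule at least monthly assessment of all patients, which partly evens out the chance of detecting an event. It does not govern which detected events are then kept.
- **Condensed article.** A toxicity scale may be named in the full protocol. That would excuse silence, but the article names a postoperative standard for all adverse events.
- **The illustration.** Its filtering is assumed and acts in one arm only. Two of its base rates come from 18 patients in another trial, and the article's own percentages for those groups do not match its counts. It shows sensitivity and does not estimate bias.
- **Open-label design.** Comparing surgery with no surgery makes unblinded attribution unavoidable, and removing the gate will not cure that.

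**Conclusion.** The concern holds in a limited form. The article states a rule under which unblinded investigators decide, with no criterion, which events enter the adverse event record, and it grades that record on a standard that does not suit chemotherapy toxicity in an arm with no operation. Following the text can filter non-serious events differently by arm.

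The effect on the secondary complication rate is an inference, reasonable for the chemotherapy component and weak for the postoperative one. Its size and direction cannot be derived from the documents. If a one-arm loss of 10% of patients with an event is assumed, with equal true rates between 60% and 81.8%, the false-positive chance would be 13.7% to 28.4% instead of 5.0%. The correction is worth making because it is cheap now and impossible once events have gone unrecorded.

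**What to change.** 1. Delete the significance gate. Record every untoward event in both arms with its date, grade and relatedness.
2. Keep the term clinically significant only for deciding whether an abnormal laboratory value is an event.
3. Grade chemotherapy events in both arms on one common toxicity scale, named in the text, and keep Clavien-Dindo for postoperative events.
4. Start the serious-event record at the same point in both arms, either consent or randomisation.
5. State that chemotherapy complications in the total complication rate are counted from this unfiltered record.
6. Acknowledge that open-label attribution of side effects leaves some bias that these changes do not remove.

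The cost is a few sentences and a case report form instruction. The downside is that more minor events will be recorded, at visits that are already scheduled.

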### Treatment Protocols

All eligible patients will be randomly divided into a test group or a control group according to a 1:1 distribution ratio. The test group will receive D2 gastrectomy plus liver radiofrequency plus postoperative chemotherapy. In the test group, only open surgery is allowed. The control group will receive chemotherapy alone. The chemotherapy regimens of the two groups are the same (11), S-1 plus cisplatin. S-1 will be given orally 80-120 mg/m² per day for the first 3 weeks of every 5-week cycle. The dose of S-1 will be given according to the patients’ body surface area (less than 1.25 m², 80 mg; 1.25–1.5 m², 100 mg; and greater than 1.5 m², 120 mg). Patients will receive cisplatin 60 mg/m² on Day 8 of every 5-week cycle *via* intravenous infusion. **Table 1** shows the treatments applied in this study. **Table 2** shows the medication and usage in this experiment. Because all enrolled patients are tested for the molecular profile of the tumors, such as HER2, PDL1, MSI and MMR expression, follow up treatment protocols could be adjusted according to the patients’ molecular profile, such as trastuzumab or immunotherapeutic antibody. Accordingly, in the statistical analysis of data, different patients also require conduct subgroup hierarchical analysis according to the molecular detection results of tumors to reduce data error.

**Table 1 T1:** The treatments applied in this study.

	gastrectomy (total gastrectomy, distal or proximal gastrectomy plus D2 lymph node dissection)	liver radiofrequency	chemotherapy (S-1 + cisplatin)
test group	√	√	√
control group	—	—	√

**Table 2 T2:** The medication and usage in this experiment.

Chemotherapy drugs	dose	Timing of the drugs (a total of 35 days/cycle)			
		Day 1-7/cycle	Day 8/cycle	Day 9-21/cycle	Day 22-35/cycle
S-1	80-120 mg/m² (oral)	√	√	√	—
cisplatin	60 mg/m² (intravenous infusion)	—	√	—	—

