### Clinical Data

Clinical data from the patients will be obtained by medical staff and recorded on an online electronic platform (http://www.medresman.org.cn) and in the CRF table. The samples will be coded, and the patients’ identity will be known only by the attending physician. The clinical data will include the following: general patient information, past medical history, past surgical history, laboratory examination results, imaging results, surgery details, PFS and OS. The timing and processing of the above recorded contents will be reflected in the CRF table, and the laboratory examinations will mainly assess preoperative and postoperative routine blood, liver function, tumor markers, and inflammatory indicators. The prognosis of GC with liver metastasis (GCLM) was very poor, with a 5-year survival rate of <10% (17). Patients will be assessed at least monthly from baseline for adverse events *via* verbal interview, physical examination, and blood tests, including a complete blood cell count and assessments of liver and renal function, until disease progression. Abdominal CT and measurements of tumor markers, such as carcinoembryonic antigen, carbohydrate antigen 199, carbohydrate antigen 125, carbohydrate antigen 153 and alpha fetoprotein, were done every 3 months.

A detailed description of the above data is shown in the CRF table. **Table 3** shows the test and data acquisition schedule for this experiment.

**Table 3 T3:** The test and data acquisition schedule for this experiment.

Stage	Pre-operation	Intra-operation	Postoperation					Unplanned follow-up
Follow up period	14-1 days		0-12 month	13-24 month	25-36 month	37-48 month	49-60 month	
Baseline data collected	√	—	—	—	—	—	—	—
Inclusion and exclusion	√	—	—	—	—	—	—	—
Sign informed consent	√	—	—	—	—	—	—	—
Group determination	√	—	—	—	—	—	—	—
Fill in the basic information	√	—	—	—	—	—	—	—
Physical examination	√	—	√	√	√	√	√	—
Imaging examination	√	—	√	√	√	√	√	if necessary
Laboratory examination	√	—	√	√	√	√	√	—
Operation information	—	√	—	—	—	—	—	—
Postoperative pathology	—	√	—	—	—	—	—	if necessary
Safety observation	√	—	√	√	√	√	√	if necessary
Record adverse events	√	—	√	√	√	√	√	if necessary
Other works	√	√	√	√	√	√	√	if necessary

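### The safety-recording windows contradict each other, and the one for serious adverse events has no starting point in the control arm

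*Protocol article*

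**What the plan says.** The adverse-event paragraph of Study Endpoints gives two windows. All adverse events, related or not, count "from the date participants sign informed consent until 5 years after the end of treatment in this study". For serious events the rule is: "The investigators will keep a full record of serious adverse events from the start of the surgery to the end of the study". The paragraph also opens with a definition that fits a start at consent poorly: "Adverse events are adverse medical events that occur after surgical and medical treatment in patients in clinical trials".

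Clinical Data gives a third: "Patients will be assessed at least monthly from baseline for adverse events", by interview, examination and blood tests, "including a complete blood cell count and assessments of liver and renal function, until disease progression". Table 3, in the same section, ticks adverse-event recording in the pre-operative column (14 to 1 days before) and in every postoperative column to month 60.

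On treatment, Treatment Protocols states: "The control group will receive chemotherapy alone". Table 1 has a dash for gastrectomy and for liver radiofrequency in that arm.

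The secondary endpoint, the total complication rate, is defined separately in Study Endpoints. It combines postoperative complications within 30 days of the procedure, graded by Clavien-Dindo, with side effects of chemotherapy, for which no period is given. The nature and severity of adverse events in general are to be assessed by the "expert consensus on diagnostic criteria for postoperative complications of gastrointestinal cancer in China".

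**The concern.** A safety comparison between randomised arms needs a clock that starts and stops in the same way in both. Here the start for serious events is an operation that one arm does not have, and the stated ends differ: progression, end of study, month 60, or 5 years after treatment. Two centres could each follow the text and collect different data.

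The end at progression matters most for the statistics. The trial hopes that the test arm will progress later. If toxicity is looked for only until progression, a treatment that works is observed for longer and collects more counted events, even when the monthly risk is the same.

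Grading is a lesser part of the same problem. The only trial treatment controls receive is chemotherapy, yet the source named for grading adverse events is a consensus on complications after surgery.

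**Working it through.** The plan states no figure on this point that could be reproduced. The check is a comparison of the texts, followed by an illustration under stated assumptions.

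**Step 1. The windows side by side**

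| Place | What it covers | Start | End |
|---|---|---|---|
| Study Endpoints | all adverse events | consent | 5 years after end of treatment |
| Study Endpoints | serious adverse events | start of surgery | end of study |
| Clinical Data | monthly assessment for adverse events | baseline | disease progression |
| Table 3 | adverse-event recording | pre-operation (14 to 1 days) | month 60 |

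No two rows agree on both start and end. Table 3 and the first row also end at different times in the test arm. Month 60 is counted from the operation and chemotherapy follows the operation, so 5 years after the end of treatment falls later than month 60.

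**Step 2. Does the serious-event window start in both arms?** In the test arm it starts at the gastrectomy and ablation. In the control arm there is no such operation. The staging laparoscopy or laparotomy in Inclusion Criteria applies to everyone, but it is unlikely to be what is meant. Table 3 places group allocation before the operation, and the causality sentence in Study Endpoints pairs the surgery with the investigational drugs. The surgical anchor recurs in the column headings of Table 3 and in Follow-up, where the first visit is on day 14 after surgery.

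**Step 3. Does the complication endpoint depend on that window?** No. Its postoperative part has its own 30-day limit and can occur only in the test arm. Its chemotherapy part has no stated period, so how long toxicity is actively looked for decides how much of it is counted.

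**Step 4. What an end at progression could do.** Assume a constant complication hazard h per month, identical in both arms, and independent exponential progression with median m months. The probability of a complication before progression is

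P = h / (h + ln2/m).

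For h = 0.10 and m = 6: ln2/6 = 0.1155, so P = 0.10/0.2155 = 46.4%. Likewise:

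| h per month | m = 6 | m = 9 | m = 12 |
|---|---|---|---|
| 0.02 | 14.8% | 20.6% | 25.7% |
| 0.05 | 30.2% | 39.4% | 46.4% |
| 0.10 | 46.4% | 56.5% | 63.4% |

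Fixed windows show the same pattern. With P = 1 − exp(−ht), observing one arm for 6 months and the other for 12 gives 11.3% against 21.3% (h = 0.02), 25.9% against 45.1% (h = 0.05) and 45.1% against 69.9% (h = 0.10).

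All values of h, m and t are assumptions, and none stands in the protocol. Chemotherapy toxicity is unlikely to have a constant hazard. The tables show direction only and forecast nothing for this trial.

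**The case against.** The strongest reply is that the passages, read together, do cover the control arm. The general window is stated without restriction by arm: adverse events "will be considered from the date participants sign informed consent until 5 years after the end of treatment in this study". Serious events are adverse events, and the same paragraph has all serious events reported whether or not they are related to drug or surgery. Follow-up has all enrolled patients examined at least monthly. This stands. A reader might infer that no control patient has a window for serious events and that such events will be lost; the documents do not support that.

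A reader might also infer that the days between consent and operation are uncovered in the test arm. Table 3 ticks both safety observation and adverse-event recording before the operation, so that inference fails too.

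A third tempting step is that the surgical start date itself biases the total complication rate. It does not, because that endpoint is defined without reference to serious adverse events.

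It can further be said that the phrase about progression ends a visit schedule and does not say that events stop counting. That is a possible reading, and Follow-up and Table 3 favour it. But Clinical Data states the limit plainly, and nothing in the article says which text prevails. Finally, the secondary objective is total incidence, so a poorly suited severity scale does not by itself make the comparison uninterpretable. That is also right; the point on grading is one of fit.

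**Conclusion.** The concern holds as an internal contradiction. The stated safety windows differ in start and end, and the one for serious adverse events has no usable start in the control arm. This is a stated rule that fails for one arm, not detail that a condensed article leaves out.

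The consequence for the total complication rate is conditional. If chemotherapy toxicity is actively assessed only until progression, and progression-free survival differs between the arms, then observation time differs and the arm with longer progression-free survival can show more complications at equal risk. The documents give neither a toxicity hazard nor the observation lengths, so the size cannot be derived.

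The matter should be corrected. It touches one of two secondary endpoints and the safety reporting. It leaves the analysis of overall survival untouched.

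**What to change.** - Reconcile the adverse-event paragraph of Study Endpoints, the assessment text in Clinical Data and Table 3 to a single window for adverse and serious adverse events. Its start must exist in both arms: consent for recording, randomisation for the comparison. Its end should be the same in both arms regardless of progression.
- Compare total complications over a fixed common period from randomisation, and also show postoperative and chemotherapy complications separately.
- Grade chemotherapy toxicity in both arms on a general toxicity scale (CTCAE, for example) instead of the postoperative-complication consensus. Clavien-Dindo can stay for surgical events, as the plan already has it.

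The cost is wording in the protocol and the case report form, with slightly more safety recording in controls and after progression. Treatment is unchanged.
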